### **6.1.3 CHANGES TO PROTOCOL DUE TO THE COVID-19 PANDEMIC**

Due to the COVID-19 pandemic, minimal adaptations to the assessment and consent procedures were implemented from March 2020 (that is, from study participant 082), as follows:

- To minimise the risk of infection, participants may no longer choose between face-to-face assessments at our clinic or video conference assessments. Instead, all assessments are performed via video conference software.
- To avoid delays, participants may be included and randomised immediately after showing the signed informed consent form to the researcher via the web camera during the inclusion assessment (i.e. before the informed consent form has reached the clinic via regular mail).

The ethics review authority will be made aware of these minor changes to the protocol, which are likely to remain in place until the end of the study.

## **6.2 RANDOMISATION, ENROLMENT AND MASKING**

Participants will be randomised at a 1:1 ratio to BIP TIC (therapist- and parent-guided internet-delivered behaviour therapy) and a control condition (therapist- and parent-guided internet-delivered education on tics). Randomisation will be conducted by one or several researchers (according to a task delegation list) using an online randomisation service (Randomize.net; set up and monitored by the Karolinska Trial Alliance [KTA; karolinskatrialliance.se/en). Randomly varying block sizes will be generated using a computer random number generator. One or several researchers (according to a task delegation list) will be responsible for the enrolment of participants and assigning participants to therapists. Participants will be informed that they will be allocated to one of two behavioural interventions for TD/Persistent (Chronic) Motor or Vocal Tic Disorder.

Assessors conducting post- and follow-up assessments will be blind to treatment allocation, for the full duration of the trial. The outcome measures are identical for both groups, ensuring that the assessors remain blind. At each follow-up assessment, participants will be reminded by their assessor to not reveal their arm allocation. To measure blinding integrity, all assessors will record whether the participating families inadvertently reveal their group allocation, and subsequently guess each participant's treatment allocation at each assessment point and motivate their choice. If the treatment allocation is accidentally revealed, that very part will be cut out of the video recording. A new blind assessor will then watch the video recording and conduct the rating that will be used in the trial. Subsequent assessments for that participant will then be conducted by a different assessor (than the first one; blind to treatment allocation), where possible. The primary analysis will be performed after the trial's final participant has finished his/her 3-month follow-up assessment (primary endpoint). Assessors will remain blind for the 6- and 12-month naturalistic follow-up assessments. The trial will end when the trial's final participant has finished his/her 12-month follow-up assessment.

In case of a medical emergency, participants will be encouraged to immediately seek appropriate health care, and to inform their therapist about this, who in turn will inform the trial coordinator. The trial coordinator will be in charge of following up the incident. This whole procedure can be done without unblinding the outcome assessors, so an emergency unblinding system is not required for the trial.

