***Trimbos/iMTA Questionnaire for Costs associated with Psychiatric Illness (TiC-P)***

The TiC-P [56] will be used to assess healthcare and societal resource use. The questionnaire includes items on healthcare resource use (e.g., healthcare visits), supportive resources (e.g., private tutoring), medications, prescription-free drugs, school absenteeism, academic productivity loss, and parental productivity loss and is frequently used in health economic studies. The TiC-P version used in the study has been adapted by the research team for the use among young people and parents. The questionnaire takes from around 5 to 15 minutes to complete, depending on the family's service use.

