## 6.5 TREATMENT

Both treatments are internet-delivered, using the BIP platform. This platform is previously developed by our research team, and is currently used in several trials. BIP is specifically designed for use by children and adolescents, and their parents, with age-appropriate appearance, animations and interactive scripts ([www.bup.se/bip](http://www.bup.se/bip)).

Each intervention consists of 10 chapters (modules), delivered over 10 weeks. During this time, participants (both the child/adolescent and the caregiver/parent) have regular contact with a trained therapist inside the platform. The therapist provides feedback, answer questions, and reminds to complete the next module if required. Communication is possible via traditional text messages (resembling e-mail) or via comments on specific worksheets. When the participant receives a message in the platform, s/he also gets an SMS reminder to her/his phone (in some cases only sent to the parent). The therapist usually logs in daily (on

workdays; at minimum every 48 hours). Therapist time is automatically logged in the platform. There are no specified limits to the therapist time, however, in our pilot trial [15], the average therapist time per participant per week was 25 minutes. Participants are typically in contact with their therapist several times a week. Phone calls are possible if the participant/therapist for a certain reason feels it is needed, but are generally kept to a minimum. The participants are welcome to contact their therapist at any time, who will reply during office hours. Telephone time is manually logged in an Excel spreadsheet by the therapist, and later entered to the trial database.

The therapist is available for 10 weeks. In certain circumstances (e.g. illness or holidays), participants can pause their therapist-support for one or two weeks, which extends the treatment length to a maximum of 12 weeks. The participants can work through the first three modules as quickly as they prefer. For the following modules, the quickest possible pace is one chapter per week. After 9 weeks, all modules will be made available for the participant (regardless of how many modules s/he has completed). After the 10-12 weeks, the child/adolescent and caregiver/parent can continue to access all treatment modules for the whole follow-up period (12 months), but without therapist-support.

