## **9.4 HANDLING OF ADVERSE EVENTS**

All adverse events will be noted by the trial coordinator in a specific log (including date, recorded clinical symptoms, and a brief description of the event), which in turn will be shared with the Karolinska Trial Alliance (KTA). The research team could be notified about adverse events in numerous ways, including through direct (text or telephone) communication with the participant, and completions of the Side effects questionnaire. Regular meetings (“ward rounds”) will be held within the research team where treatment progress and potential adverse events are discussed. High scores on SMFQ (depressive symptoms) including its additional suicide item, might also be indicators of adverse events. Scores above 13 points, or

scores of 2 or 3 points on the suicide item, will automatically raise a flag in the BASS system, to directly notify members of the research team to follow this up (via the telephone) with the participant.

SAEs and SUSARs will be recorded in the patient's medical record (Take Care), in ELN, as well as in the trial coordinator's log. Appropriate action will be taken in the case of SAE and SUSAR, making sure the participant will get in contact with suitable health care services. Events will be considered as potentially treatment-related up to the 3-month follow-up, where the reporting of adverse events will terminate.

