### **9.5 REPORTING OF ADVERSE EVENTS**

As mentioned above, AEs and SAEs may be reported through various sources. Here follows a more detailed description of how the various sources will be combined when reporting AEs and SAEs in the resulting publications:

- 1) AEs/SAEs may be reported to the therapist or the researcher through communication with the participants.
- 2) AEs are also recorded through completion of the SMFQ. SMFQ data collected at baseline, 5 weeks into treatment, post-treatment and the 3-month follow-up will be used for AE reporting purposes. Any total score >13 or score >1 at the additional suicide item, at 5 weeks into treatment, post-treatment or the 3-month follow-up, is recorded as an AE **if** it is greater than their baseline score. Only the child version of the SMFQ will be used for AE reporting.
- 3) AEs are also recorded through the Side effects questionnaire completed at baseline, 5 weeks into treatment, post-treatment and the 3-month follow-up. A score on any item that is equal-to-or-greater-than 2 ("about half the time") **and** greater than their baseline score is recorded as an AE. The Side effects questionnaire is completed by the parent.

The listed sources above will be combined and AEs will be summarized by number (frequencies and percentages), nature, severity and whether they are expected or unexpected. If there are any SAEs, the trial coordinator and the PI will judge whether these are related to the treatments provided. No statistical tests comparing the treatment groups will be performed.

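### The emergency route names only the therapist, whose support ends at week 10–12, while AE reporting runs to the 3-month follow-up; healthcare-use data collected in that period are not listed as an AE source

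*Combined protocol and SAP*

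**What the plan says.** **Emergency route.** Protocol section 6.2, in explaining why emergency unblinding is not needed, says that "participants will be encouraged to immediately seek appropriate health care, and to inform their therapist about this, who in turn will inform the trial coordinator". It names no other contact.

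**Therapist availability.** Section 6.5 states: "The therapist is available for 10 weeks". In circumstances that include illness, "participants can pause their therapist-support for one or two weeks, which extends the treatment length to a maximum of 12 weeks". Afterwards families keep the modules "for the whole follow-up period (12 months), but without therapist-support". Section 12 (ethical considerations) says instead that each participant has a dedicated therapist, and that participant and therapist stay in close contact, for the whole trial, so that adverse reactions are noticed.

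**AE window.** Section 9.4: "Events will be considered as potentially treatment-related up to the 3-month follow-up", at which point AE reporting stops.

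**AE sources.** Section 9.5 combines three. The first is spontaneous report: "AEs/SAEs may be reported to the therapist or the researcher through communication with the participants". The others are the child SMFQ and the parent-completed Side effects questionnaire. Section 9.4 leaves the list of ways to notify the research team open, and includes direct text or telephone contact. SAP 4.13 summarises AEs at 5 weeks, post-treatment and 3FU, and refers to the protocol for how they are collected.

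**Other data on health events.** TiC-P "will be used to assess healthcare and societal resource use". Table 1 schedules it at baseline, post-treatment, 3FU and the later follow-ups. The concomitant-interventions interview is held at post-treatment and every follow-up. Section 9.5 names neither.

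**The concern.** The only contact that families are told to inform in an emergency stops supporting them well before the AE window closes. The protocol does not say who replaces the therapist between then and 3FU, and section 12 gives safety assurances that rest on therapist contact continuing.

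The same period is thin on structured SAE capture. Hospitalisation is an SAE criterion in Table 2, but neither questionnaire listed in section 9.5 is described as asking about it. Two instruments that touch on healthcare use are completed in both arms at post-treatment and 3FU, yet the plan gives them no path into the AE log.

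What is at stake is the completeness of the safety record. Section 6.9 keeps outcome data out of stopping decisions and makes SAE review the stated safety trigger, and the published AE tables draw on the same sources. The primary efficacy comparison is not affected.

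**Working it through.** The plan gives no figure on this point to reproduce. The check has two parts.

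**1. Length of the gap**

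Inputs:
- Therapist support ends at week S = 10, or S = 12 after a two-week pause (section 6.5).
- 3FU falls at 3 months, with a window of −1/+2 months, so at 2 to 5 months (section 6.6.3).
- One month = 365.25/12/7 = 4.35 weeks, so F = 8.7, 13.0 or 21.7 weeks for 2, 3 or 5 months.
- Assumption: the AE window L runs from the start of treatment to 3FU. Paused weeks count as supported, which makes the gap look smaller.

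Share without therapist support = (L − S)/L.

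| Reading | 3FU at 2 months | at 3 months | at 5 months |
|---|---|---|---|
| S = 10, L = 10 + F | 8.7/18.7 = 47% | 13.0/23.0 = 57% | 21.7/31.7 = 68% |
| S = 12, follow-up timed from week 12, L = 12 + F | 8.7/20.7 = 42% | 13.0/25.0 = 52% | 21.7/33.7 = 64% |
| S = 12, follow-up timed from week 10, L = 10 + F | 6.7/18.7 = 36% | 11.0/23.0 = 48% | 19.7/31.7 = 62% |

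The third row is included because section 6.6.3 counts follow-up from the end of the 10-week treatment, which leaves the timing after a pause unclear. The nominal value is 57% and the full range is 36% to 68%.

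**2. How a hospital admission after the end of support could reach the AE log**

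- *Therapist:* named in section 6.2, but support has ended under section 6.5.
- *Researcher or research team:* open under sections 9.4 and 9.5, but the family must volunteer the report. Section 6.2 does not direct them there.
- *Child SMFQ:* completed at post-treatment and 3FU. High totals or suicide-item scores raise an automatic flag (section 9.4). It covers mood and suicidality, not admissions.
- *Side effects questionnaire:* 17 short items on common complaints (section 5.5.5), at the same two time points.
- *Assessor contact at post-treatment and 3FU:* an admission may be mentioned here. Whether the assessor passes it on as an AE is not stated.
- *TiC-P:* covers healthcare visits and medication (section 5.5.5). It is assigned to the economic evaluation (section 8.3, SAP 5.2) and not listed in section 9.5.
- *Concomitant-interventions interview:* covers medication with its indication and dates, and psychological treatment (section 5.5.3). It is not listed in section 9.5.

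So after support ends, an admission that does not show in mood or common symptoms depends on unprompted communication or on what happens to come up at two assessments. These are 3 months apart at nominal timing. They can be up to 5 months apart if post-treatment follows at once and 3FU is at its latest.

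**The case against.** The strongest reply is that section 6.2 is not the SAE procedure. It is a masking paragraph, and section 9 governs capture. Section 9.5 accepts reports to the researcher as well as the therapist, section 9.4 leaves the routes open, SMFQ flags lead to a telephone call, and assessors speak with families at post-treatment and 3FU. Participants also stay registered at the research clinic to 12 months (section 5.2). All of this stands, and it rules out several stronger readings that a reader might draw:

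- *That SAEs are routed only through the therapist.* Section 9.5 says otherwise. Only the emergency instruction is limited in this way.
- *That 57%, or 36% to 68%, of SAEs would be missed.* The figures measure calendar time without therapist support. Other routes stay open, and the documents give no SAE rate.
- *That TiC-P would show an SAE.* It is described by examples and by frequencies of use. No hospitalisation item, recall period or reason for contact is stated. It could show one; the documents do not establish that it would.
- *That the section 6.9 review sees only logged events, or that the published SAE count will be too low.* Section 6.9 does not say how SAEs come to the review, so an undercount is a possibility and not a finding.
- *That the interview is excluded as a source.* What a family tells an assessor could count as communication with the researcher. Its use is unspecified.

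It is also fair to say that AE reporting is descriptive and identical in both arms, so no bias in the primary comparison is shown. None of this settles who receives an emergency report after week 10–12, or removes the conflict between sections 6.5 and 12.

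**Conclusion.** The concern holds in a limited form. The emergency instruction depends on a contact whose support ends before the AE window does, and sections 6.5 and 12 contradict each other on how long that contact lasts. About 57% of the window at nominal timing, and between 36% and 68% across the stated windows and readings, is without therapist support. This rests on the AE window starting with treatment and on the two possible ways of timing follow-up after a pause.

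Section 9.5 also leaves out two instruments, already collected at both relevant time points, that could reveal an SAE. How many events they would add cannot be judged without seeing the adapted TiC-P. The gap concerns the clarity and completeness of safety capture. It is worth correcting because the correction is cheap, not because the documents show that SAEs are being lost.

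**What to change.** 1. Reconcile protocol sections 6.2, 6.5, 9.4, 9.5 and 12 on who receives emergency and SAE reports from the end of therapist support (and during a pause) to 3FU. Which statement is right is for the investigator and sponsor to decide; no clinical rule is proposed here.
2. In section 9.5 and SAP 4.13, add the post-treatment and 3FU entries from TiC-P and the concomitant-interventions interview as a further AE/SAE source. A research-team member who is not a blind assessor screens them against Table 2 as they arrive. Entries already collected are screened before the stage 1 database lock.
3. First check whether the adapted TiC-P has a hospitalisation item and a recall period, and record the answer, because the yield depends on it.

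**Cost.** Wording changes, plus reading two existing forms at two time points: at most 220 × 2 × 2 = 880 entries. No new visit, measure or staff role is needed. The drawback is that minor healthcare contacts must be read and dismissed, and the yield may be small.

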## **6.3 ASSESSMENT POINTS FOR EACH OUTCOME**

**Table 1.** Assessment points for each outcome.

| Outcome \ Assessment point                              | Screening                           | Baseline | Mid-treatment | Post-treatment | 3-month follow-up (primary endpoint) | 6-month follow-up | 12-month follow-up        |
|---------------------------------------------------------|-------------------------------------|----------|---------------|----------------|--------------------------------------|-------------------|---------------------------|
| Screening/Baseline measures                      |                                     |          |               |                |                                      |                   |                           |
| Self-referral questionnaire (child- or parent-reported) | X (self-referred participants only) |          |               |                |                                      |                   |                           |
| Demographic data (clinician-entered)                    |                                     | X        |               |                |                                      |                   |                           |
| Demographic data (parent-reported)                      |                                     | X        |               |                |                                      |                   |                           |
| MINI-KID (clinician-administered)                       |                                     | X        |               |                |                                      |                   |                           |
| OCD-RD (clinician-administered)                         |                                     | X        |               |                |                                      |                   |                           |
| AQ-10 (parent-reported)                                 |                                     | X        |               |                |                                      |                   |                           |
| SNAP-IV (parent-reported)                               |                                     | X        |               |                |                                      |                   |                           |
| PUTS (child-reported)                                   |                                     | X        |               |                |                                      |                   |                           |
| Clinician-rated/entered outcomes                 |                                     |          |               |                |                                      |                   |                           |
| YGSS symptom checklist                                  |                                     | X        |               | X              | X                                    | X                 | X                         |
| YGSS TTSS (primary outcome measure)                     |                                     | X        |               | X              | X                                    | X                 | X                         |
| YGSS Impairment                                         |                                     | X        |               | X              | X                                    | X                 | X                         |
| CGI-S                                                   |                                     | X        |               | X              | X                                    | X                 | X                         |
| CGI-I                                                   |                                     |          |               | X              | X                                    | X                 | X                         |
| CGAS                                                    |                                     | X        |               | X              | X                                    | X                 | X                         |
| iiPAS                                                   |                                     |          | After 5 weeks | X              |                                      |                   |                           |
| Concomitant interventions                               |                                     |          |               | X              | X                                    | X                 | X                         |
| Blindness checks                                        |                                     |          |               | X              | X                                    | X                 | X                         |
| Did the participant meet the therapist?                 |                                     |          |               | X              |                                      |                   |                           |
| BIP platform usage data + therapist telephone time      |                                     |          |               | X              |                                      |                   | X (Number of logins only) |
| Assessment format (face-to-face or video conference)    |                                     | X        |               | X              | X                                    | X                 | X                         |
| Child-reported outcomes                          |                                     |          |               |                |                                      |                   |                           |

|                                                               |  |   |               |   |   |   |   |
|---------------------------------------------------------------|--|---|---------------|---|---|---|---|
| C&A GTS-QOL 6-12 or 13-18, depending on the participant's age |  | X |               | X | X | X | X |
| SMFQ Child + additional suicide item                          |  | X | After 5 weeks | X | X | X | X |
| OCI-CV                                                        |  | X |               | X | X | X | X |
| Treatment credibility                                         |  |   | After 3 weeks |   |   |   |   |
| WAI-C                                                         |  |   | After 3 weeks |   |   |   |   |
| Treatment satisfaction                                        |  |   |               |   | X |   |   |
| Need for further treatment                                    |  |   |               |   | X |   |   |
| KIDSCREEN-10 child                                            |  | X |               | X | X | X | X |
| Caregiver/parent-reported                              |  |   |               |   |   |   |   |
| PTQ                                                           |  | X | After 5 weeks | X | X | X | X |
| SMFQ Parent                                                   |  | X | After 5 weeks | X | X | X | X |
| Side effects questionnaire                                    |  | X | After 5 weeks | X | X |   |   |
| Treatment credibility                                         |  |   | After 3 weeks |   |   |   |   |
| WAI-P                                                         |  |   | After 3 weeks |   |   |   |   |
| Treatment satisfaction                                        |  |   |               |   | X |   |   |
| Need for further treatment                                    |  |   |               |   | X |   |   |
| KIDSCREEN-10 parent                                           |  | X |               | X | X | X | X |
| TiC-P                                                         |  | X |               | X | X | X | X |

**Note:** For full names of abbreviations, see section 5.5.

